### Safety aspects

Robotic-assisted radical prostatectomy is a highly technically demanding procedure. High-volume surgeons with great experience have better results than low-volume surgeons with less experience [32].

To avoid bias based on the learning curve of the surgeons, every surgical procedure will be performed by a senior surgeon who has experience with at least 100 robotic-assisted radical prostatectomies. Administration of tranexamic acid at the beginning of the procedure by an anesthesiologist is a simple common procedure, performed on a routine basis, and no special training is necessary, and no complications are expected.

### Data collection

A daily visit of the study patients will be made by clinical investigators or a delegated physician. All protocol-required information collected during the trial will be entered into the patient’s record form.

Patient identification on the case report form (CRF) is through their unique trial identifier, allocated at the time of recruitment. Data coding will be carried out at various stages during the study. The patient’s record form is subject to audit by the principal investigator (PI) and Institutional Review Board (IRB).

Preoperative data gathered include patient age, body mass index, American Society of Anesthesiologists physical status classification system score, and comorbidities. Intraoperative data to be collected include surgery duration (skin to skin), console time (console surgeon activity time), and weight of the prostate.

Laboratory tests will include blood cell count (BCC), hematocrit test, and plasmatic creatinine level at the beginning of the procedure, 3–6 h after the procedure, on POD 1, POD 2, and POD 7 in the morning.

The differences between the hematocrit and hemoglobin levels (eventually weighted for the grams of the prostatic tissue) and hemoglobin/creatinine ratios will be obtained.

The volume of the fluids in the drain will be measured on postoperative day 1, and if the volume does not exceed 200 ml for 24 h, the drain is extracted. If the volume will be higher than 200 ml/24 h and the creatinine level in the drain fluid exceeds 500 μmol/l, urinary leakage will be confirmed (29). Patients with confirmed urinary leakage or urinoma will be excluded from the evaluation.

Postoperative course assessments will include duration of intermediate/intensive care, hospital stay including readmissions for postoperative complications, reinterventions (reoperations, endoscopic and interventional radiology procedures), the reasons for readmissions, and transfusion rates. The patients will be seen by a clinical investigator 3 months after the surgery in an outpatient fashion. The evidence of complication and level of prostatic specific antigen (PSA) will be monitored. Upon completion of 200 patients, the statistical processing will be performed, and results will be unblinded.

All study-related information will be stored securely at the study site. All participant information will be stored in locked file cabinets in areas with limited access. All reports, data collections, processes, and administrative forms will be identified by a coded ID number only to maintain participant confidentiality. All records that contain names or other personal identifiers will be stored separately from study records identified by code number.

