### Primary and secondary endpoints

The primary endpoint is to analyze the effect of tranexamic acid on perioperative and postoperative blood loss in a randomized and prospective manner. A clinically significant difference between the groups on POD 1 is set to 10 g/l. The sample size was calculated for this setting.

The additional aim of the RARPEX trial is to analyze the effect of tranexamic acid on other postoperative complications: wound infection, intraabdominal collections, urinary leakage, delayed gastro-intestinal emptying, postoperative hemorrhage, pneumonia, and abdominal rupture, especially analyzing the incidence of cardiac events and venous thromboembolism (VTE) after the procedure (Table 1).

**Table 1 Tab1:** Clinical parameters and postoperative complications for analysis

Parameters	Definitions
Hospital stay	Days from initial operation to hospital discharge plus any readmission within 30 days
Console time	Time of console surgeon activity (min)
Postoperative hemorrhage	Evidence of blood loss from drains, based on ultrasonography or CT
Transfusion rate	The number of blood transfusions
Urinary leakage	Evidence of creatinine level > 500 μmol/l and volume of the drain output exceeds 200 ml/24 h, confirmed on cystography
Lymphorrhea	Evidence of creatinine level < 500 μmol/l, hematocrit < 0.2, and volume of the drain output exceeding 200 ml/24 h, no urinary leakage on cystography
Intraabdominal fluid collection	Collection of fluid measuring ≥ 3 cm associated with clinical or laboratory abnormalities
Symptomatic fluidothorax	Fluid in the pleural cavity associated with respiratory distress or a need to evacuate the fluid
Thromboembolism	Unilateral limb swelling, acute respiratory insufficiency, based on ultrasonography or CT
Myocardial infarction	Increase of serum concentration of CK-MB and troponin and/or the following ECG changes: new Q waves ≥ 0.04 in duration, new persistent ST elevation, and/or depression
Brain stroke	Presence of neurological symptoms, findings on CT scan or MRI
Pneumonia	Presence of a new infiltrate on chest X-ray, as well as the following: body temperature > 38 °C, abnormal elevation of WBC, or positive sputum, and requiring antibiotic treatment
Acute renal failure	Serum creatinine > 300 μmol/l and/or need for dialysis
Wound infection	Surgical site infection associated with laparotomy that develops during the initial hospital stay

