## Statistical methods

Each patient’s allocation to the analyzed population will be defined prior to the analysis and will be documented. In the full analysis set, patients will be analyzed as randomized according to the intention-to-treat principle. The intention-to-treat principle implies that the analysis includes all randomized patients. The per-protocol analysis set will include all the patients without major protocol deviation. Deviations from the protocol will be assessed as major or minor. Patients with major deviations from the protocol will be excluded from the protocol analysis. The safety analysis set will analyze the patients according to the treatment. The null hypothesis assumes that there is no difference in the hemoglobin level drop after the procedure in both groups. We will use a two-sample *T* tests allowing unequal variance with respect to the endpoint, which is the drop of hemoglobin levels. Differences between age and PSA will be assessed by the non-parametric Mann-Whitney *U* test. BMI and specimen weight will be compared by the Kolmogorov-Smirnov test. A *P*-value < 0.05 will be considered statistically significant. Statistical analyses will be performed using the NCSS statistical software (NCSS, Kaysville, UT, USA).

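### The exclusion of patients with urinary leakage or urinoma conflicts with leakage being a complication outcome and with the analysis sets, because the protocol does not say which analysis it applies to

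*Protocol article*

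**What the plan says.** Three parts of the protocol article bear on this.

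- **Primary and secondary endpoints.** The additional aim is the effect of tranexamic acid on complications, listed as "wound infection, intraabdominal collections, urinary leakage, delayed gastro-intestinal emptying, postoperative hemorrhage, pneumonia, and abdominal rupture", with emphasis on cardiac events and venous thromboembolism. Table 1 is headed "Clinical parameters and postoperative complications for analysis". It defines urinary leakage as "Evidence of creatinine level > 500 μmol/l and volume of the drain output exceeds 200 ml/24 h, confirmed on cystography" and intraabdominal fluid collection as "Collection of fluid measuring ≥ 3 cm associated with clinical or laboratory abnormalities".
- **Data collection.** If drain output is above 200 ml/24 h and "the creatinine level in the drain fluid exceeds 500 μmol/l, urinary leakage will be confirmed". The next sentence reads "Patients with confirmed urinary leakage or urinoma will be excluded from the evaluation". The Study treatment section gives the same drain criteria without the exclusion.
- **Statistical methods.** The full analysis set follows intention to treat and holds every randomized patient. The per-protocol set drops patients with major protocol deviations. On safety: "The safety analysis set will analyze the patients according to the treatment". The leakage exclusion is not mentioned.

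**The concern.** Leakage is an outcome to be compared between arms, and it is also a reason, arising after randomization, for taking a patient out. If the exclusion governs the complication analysis, having the event is what removes the patient from the table meant to count it. The comparison would then show no leakage in either arm whether or not the drug has an effect.

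A patient with a leak may also have a collection, an infection, a readmission, a reintervention or a thromboembolic event. These would leave the comparison with the patient, and complication severity would be understated among those who remain. The additional objective is complications and safety, and the protocol itself concedes that its power for safety may be insufficient. Losing complicated patients from that comparison makes this worse.

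**Working it through.** The check is a comparison of texts. The protocol gives no leakage rate or expected number of leaks, so there is no figure to reproduce. The sample size calculation concerns hemoglobin and does not enter.

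**1. Does the exclusion cover every outcome case?**
- Data collection trigger: drain output > 200 ml/24 h and drain creatinine > 500 μmol/l.
- Table 1 outcome: the same two limits, plus confirmation on cystography.

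The Table 1 definition is the trigger with one more condition, so every Table 1 case is also an excluded case. The reverse does not hold. A patient who meets the drain limits but has a negative cystography is excluded without being a Table 1 leak.

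**2. What remains to be counted if the exclusion is applied literally?**
Leaks in the evaluated set = Table 1 cases minus excluded cases = 0 in each arm, for any pair of true rates. This step needs no assumed rate.

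**3. What else leaves with these patients?**
A urinoma of at least 3 cm with clinical or laboratory abnormalities meets the Table 1 definition of an intraabdominal collection. That row loses those cases but keeps collections of other origin. Any other Table 1 event in an excluded patient also leaves the comparison.

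**4. Do the analysis sets agree with the exclusion?**
- Full analysis set: all randomized patients. This contradicts the exclusion.
- Safety set: by treatment, with no leakage exclusion stated.
- Per-protocol set: removal for major deviations. Leakage is a postoperative event, and it is not among the non-standard procedures listed under Criteria for discontinuing.

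No stated set carries the exclusion, and nothing says which section prevails.

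**5. How many patients could this concern?**
Only an assumption can answer. With 200 patients enrolled, the expected number is 200 × rate. Assumed overall rates of 1%, 2%, 5% and 10% give 2, 4, 10 and 20 patients. This range shows scale only.

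**The case against.** The strongest reply is that the exclusion was never meant to reach the complication analysis. The protocol does not define what evaluation means. The sentence follows the text on laboratory tests, hemoglobin and hematocrit differences, and drain volume and creatinine. It comes before the separate paragraph on readmissions, reinterventions and transfusion. A rule limited to laboratory or drain measures is therefore plausible. Statistical methods points the same way: if its full analysis and safety sets govern, leakage can be counted and the remedy is largely what that section already says.

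This stands as a reason not to read the endpoint as certainly empty. A reader might infer that leakage must come out as zero in both arms. The documents support that only if the Data collection sentence is applied literally and overrides Statistical methods. The reply does not remove the conflict, however, because no text limits the exclusion to one measure or one set. If the narrow reading was intended, the sentence still needs correcting.

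A reader might also infer that these patients' complications would go unrecorded. The documents do not support that. Adverse events are to be recorded and graded, serious ones reported to the principal investigator, and all followed until stabilized or resolved. What could be lost is their place in the comparison between arms.

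Finally, complications are an additional aim, and the protocol stresses cardiac events and thromboembolism rather than leakage. That limits the weight of the point but does not answer it.

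**Conclusion.** The conflict is real and can be seen from the wording alone. Data collection, Primary and secondary endpoints, and Statistical methods cannot all be followed for a patient with confirmed leakage or urinoma. Under the literal reading, the leakage outcome has no countable cases in either arm at any true rate, and these patients' other complications drop out of the comparison. Under the reading favoured by Statistical methods, neither happens. The protocol does not say which applies.

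The zero count rests on one assumption, that the exclusion is applied to the complication analysis as written. No confidence limit for zero events is offered. It would depend on the number evaluable per arm, and the documents give no leakage rate to set it against.

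This concerns an additional objective and should be settled before unblinding. Who enters the primary hemoglobin comparison is a separate question.

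**What to change.** Amend the sentence in Data collection so that:

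- patients with leakage or urinoma stay in the full analysis and safety sets;
- the leak is counted by arm under urinary leakage, and under intraabdominal collection where that definition is met;
- all their other complications are counted by arm;
- if leakage is thought to disturb a laboratory or drain measure, any exclusion is confined to a sensitivity analysis that names the measure.

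Use one outcome definition of leakage in Study treatment, Data collection and Table 1. At present only Table 1 asks for cystography, and the sponsor should state which version applies. Study treatment also excludes patients with rectal or bowel injury from an equally undefined evaluation, so the same clarification should say which analysis that rule concerns.

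The protocol already commits to defining and documenting each patient's analysis population before the analysis, so the change fits there or in a short amendment. It costs a few sentences. Drain output and creatinine, the POD 7 ultrasound and the 3-month visit are already planned; cystography appears only in the Table 1 definitions. The small downside is that reported complication rates will look less favourable.

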### Data monitoring

The trial will be monitored by the principal investigator (PI) and Institutional Review Board (IRB) without additional monitoring by an Independent Safety Monitor or Data Safety Monitoring Board. The patient’s CRF is a subject to audit by the PI and IRB. Data integrity and study credibility depend on factors such as ensuring adherence to the protocol and using quality control measures to establish and maintain high standards for data quality. To ensure that accurate, complete, and reliable data are collected. The PI provides training to the site staff in the format of investigator meetings. The data are validated, and discrepancy reports are generated following data entry to identify discrepancies, such as out-of-range values, inconsistencies, or protocol deviations based on data validation checks. The PI will be actively involved in reviewing the progress of each participant on protocol and will report, to the IRB, adverse events and unexpected problems that may influence the IRB’s decision to allow the trial to continue (in accordance with the IRB’s policies). The IRB is convened to carry out reviews of the data at staged intervals during the study. The dropout rate is expected to be negligible with little or no missing data for the primary outcome measure. Standard approaches will be used to detect patterns in missing data for the other outcomes. Monitoring activities and changes to the study emanating from the monitoring activities will be described in the annual progress report.

#### Adverse event reporting and harms

Adverse events (AE) reported by the patient or by the investigator will be recorded and scored according to the NCI Common Terminology Criteria for Adverse Events (CTCAE). If AE happen during the experimental treatment period, all the details will be notified in the CRF as the time of occurrence, clinical symptoms and signs, degree, duration, and causal relationship with the treatment. In case of serious adverse events (SAE), the investigator has to inform the PI within 2 h after finding the SAE at the latest. The investigator may stop immediately the treatment if it is considered in the best interest of the patient. The imputability of the SAE with the experimental must be established. SAE with a doubtful, possible, probable, or highly probable consequence of tranexamic acid administration will be considered as associated to it. If SAE are unexpected, they will be designed as suspected serious adverse reactions (SUSARs). In this case, the PI has to declare it to the ethical committee and IRB. This must occur not later than 15 days after the first knowledge of the SAE. In case of fatal or self-threatening cases, the delay will be reduced to a maximum of 7 days and 8 days supplementary for the report completion. Once a year, the PI will create a report with the complete list of SAE that could be associated to the experimental medication including expected and unexpected effects, and a precise and critical analysis of the safety of participants included in the study.

The IRB of the study will systematically meet every 12 months after the beginning of the trial and will decide whether or not to continue the study.

#### Ancillary and post-trial care

Standard care is provided after participants have finished the study. All adverse events or reactions will be followed until stabilized or resolved.

#### Interim analyses

No interim analysis has been planned for this study.

#### Protocol amendments

All the modifications needing substantial amendments will be discussed within the IRB and ethical committee. The modifications must be accepted by these instances. Once accepted, modifications will be notified in trial registries and documents. Patients included in the study will be informed on important protocol modifications if personally relevant to them.

### Primary and secondary endpoints

The primary endpoint is to analyze the effect of tranexamic acid on perioperative and postoperative blood loss in a randomized and prospective manner. A clinically significant difference between the groups on POD 1 is set to 10 g/l. The sample size was calculated for this setting.

The additional aim of the RARPEX trial is to analyze the effect of tranexamic acid on other postoperative complications: wound infection, intraabdominal collections, urinary leakage, delayed gastro-intestinal emptying, postoperative hemorrhage, pneumonia, and abdominal rupture, especially analyzing the incidence of cardiac events and venous thromboembolism (VTE) after the procedure (Table 1).

**Table 1 Tab1:** Clinical parameters and postoperative complications for analysis

Parameters	Definitions
Hospital stay	Days from initial operation to hospital discharge plus any readmission within 30 days
Console time	Time of console surgeon activity (min)
Postoperative hemorrhage	Evidence of blood loss from drains, based on ultrasonography or CT
Transfusion rate	The number of blood transfusions
Urinary leakage	Evidence of creatinine level > 500 μmol/l and volume of the drain output exceeds 200 ml/24 h, confirmed on cystography
Lymphorrhea	Evidence of creatinine level < 500 μmol/l, hematocrit < 0.2, and volume of the drain output exceeding 200 ml/24 h, no urinary leakage on cystography
Intraabdominal fluid collection	Collection of fluid measuring ≥ 3 cm associated with clinical or laboratory abnormalities
Symptomatic fluidothorax	Fluid in the pleural cavity associated with respiratory distress or a need to evacuate the fluid
Thromboembolism	Unilateral limb swelling, acute respiratory insufficiency, based on ultrasonography or CT
Myocardial infarction	Increase of serum concentration of CK-MB and troponin and/or the following ECG changes: new Q waves ≥ 0.04 in duration, new persistent ST elevation, and/or depression
Brain stroke	Presence of neurological symptoms, findings on CT scan or MRI
Pneumonia	Presence of a new infiltrate on chest X-ray, as well as the following: body temperature > 38 °C, abnormal elevation of WBC, or positive sputum, and requiring antibiotic treatment
Acute renal failure	Serum creatinine > 300 μmol/l and/or need for dialysis
Wound infection	Surgical site infection associated with laparotomy that develops during the initial hospital stay
Urinary tract infection	Culture-positive urine, pyuria, or bacteriuria on urinalysis requiring antibiotic treatment

*CK-MB* creatine kinase MB isoenzyme, *ECG* electrocardiogram, *WBC* white blood cells, *CT* computer tomography, *MRI* magnetic resonance imaging

Postoperative complications are graded based on severity according to the Clavien-Dindo definition (Table 2) [33].

**Table 2 Tab2:** Complication grades according to the Dindo-Clavien classification scheme

Grade	Definition
Grade I	Any deviation from the normal postoperative course without the need for pharmacological treatment or surgical, endoscopic, and radiologic intervention
Grade II	Requiring pharmacological treatment with drugs other than those allowed for grade I complications
Grade III	Requiring surgical, endoscopic, or radiological intervention
Grade IIIa	Intervention not under general anesthesia
Grade IIIb	Intervention under general anesthesia
Grade IV	Life-threatening complications requiring intensive care unit management
Grade IVa	Single-organ dysfunction
Grade IVb	Multiorgan dysfunction
Grade V	Death of the patient

We plan to seek for adverse events with repetitive blood sampling and imaging to prevent the underreported frequency of these events. But we are aware that the incidence is low, and our data will might not have sufficient power to make a definitive conclusion about safety.

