### Study treatment

Based on the literature [16–18], and our pilot study [29], we decided to administer a single dose of tranexamic acid, corresponding to 20 mg/kg in 100 ml saline to all patients in the treatment group 1 at the beginning of the procedure. In the control group 2, we administer only 100 ml saline as placebo.

For prophylaxis of venous thromboembolism (according to the rules of our institution), the combination of mechanical device (graduated compression stockings) and pharmacologic agents (low-molecular weight heparin (LMWH)) in both treatment groups will be used. The prophylactic dose of LMWH is administered in the evening before the procedure, and the next dose at least 8 h after the procedure and then every evening at least till POD 7. Antibiotic prophylaxis is provided by a single dose of potent aminopenicillin as recommended by the antibiotic center: fluoroquinolone in patients with an allergy to aminopenicillin. During the procedure, the console time and weight of the prostate are monitored. Relevant concomitant care and interventions are permitted if necessary.

The surgical technique is standardized and has been described previously [30]. Standard robotic-assisted radical prostatectomy without pelvic lymphadenectomy using DaVinci Xi surgical system is performed. The dorsal vein complex (DVC) is sutured at the beginning of the procedure with two rounds of resorbable monofilament suture. To accelerate the return of continence, a modified Rocco stitch is performed in all patients. The anastomosis is performed by two tied V-loc stitches. No additional manipulation, such as fibrin glue or reinforcement with meshes, is allowed. Patients with rectal or bowel injury during the procedure will be excluded from evaluation.

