For 3 h after the procedure, patients of both groups will stay in the intermediate care unit; after moving to the standard ward, blood samples will be obtained. On POD 1, all the patients will start with mobilization and solid food intake. The volume of the fluids in the drain will be measured on postoperative day 1, and if the volume will not exceed 200 ml for 24 h, the drain will be extracted. If the volume is higher than 200 ml/24 h and the creatinine level in drain fluid exceeds 500 μmol/l, urinary leakage will be confirmed [31]. On POD 2, the patients will be released for home care with an indwelling permanent urinary catheter. On POD 7, the urinary catheter and skin sutures will be extracted, and the blood sampling and ultrasound of the lower abdomen will be performed. Three months after the procedure, a follow-up visit is scheduled. The evidence of complication and level of prostatic specific antigen (PSA) is monitored.

Upon completion in 200 patients, the statistical processing will be performed, and patients will be unblinded.

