### Minimizing treatment bias

Administration of tranexamic acid at the beginning of the procedure by an anesthesiologist is a simple common procedure, performed on a routine basis, which eliminates a learning curve.

All patients will undergo robotic-assisted radical prostatectomy without pelvic lymphadenectomy using the same technique. All surgeons participating in the study are familiar with this procedure. The dorsal vein complex (DVC) will be sutured at the beginning of the procedure.

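### The Table 1 definition of wound infection (laparotomy-related, during the initial stay) does not fit a robotic operation with planned discharge on POD 2, so port-site and post-discharge infections do not count in that outcome

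*Protocol article*

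**What the plan says.** The definition is in Table 1, under Primary and secondary endpoints of the protocol article: "Surgical site infection associated with laparotomy that develops during the initial hospital stay". Both conditions, the type of incision and the time window, have to be met.

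The same section makes wound infection part of the additional aim, which is to "analyze the effect of tranexamic acid on other postoperative complications: wound infection, intraabdominal collections, urinary leakage" and further events.

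Other sections fix the operation and the calendar:

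- **Operation.** Study treatment: "Standard robotic-assisted radical prostatectomy without pelvic lymphadenectomy using DaVinci Xi surgical system is performed". Minimizing treatment bias: "All patients will undergo robotic-assisted radical prostatectomy without pelvic lymphadenectomy using the same technique".
- **Discharge.** Study treatment: "On POD 2, the patients will be released for home care with an indwelling permanent urinary catheter".
- **First planned visit after discharge.** Study treatment: "On POD 7, the urinary catheter and skin sutures will be extracted".
- **Later follow-up.** Data collection: "The patients will be seen by a clinical investigator 3 months after the surgery in an outpatient fashion". Complications are to be monitored at that visit.
- **Another window in the same table.** The hospital stay row counts "Days from initial operation to hospital discharge plus any readmission within 30 days".

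**The concern.** The definition reads as if written for open surgery with a longer admission. In this trial the wounds are those of a robotic procedure, and the planned stay ends while the skin sutures are still in place. An infected port site seen at suture removal, or one that brings the patient back to hospital, would not be a wound infection under Table 1. The readmitted patient would add days to the hospital stay row and still count as free of wound infection.

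What is at stake is the meaning of one secondary outcome. If few or no events qualify in either arm, the cause could be the wording of the row and not an absence of infections, and the published table would not let a reader tell which. The section also says that events are to be sought actively so that they are not under-reported, and this row works against that aim.

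**Working it through.** The plan states no wound infection rate, event count or power, so there is no figure to reproduce. The check has two parts.

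**1. The definition against the trial's own procedures**

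| Condition in Table 1 | What the article plans | Consequence, read literally |
|---|---|---|
| Linked to a laparotomy | One robotic technique for all patients; no laparotomy described (Study treatment; Minimizing treatment bias) | Port-site infections do not qualify |
| Arises in the initial stay | Planned discharge on POD 2 (Study treatment) | Infections first appearing at home, at the POD 7 visit, on readmission or by 3 months do not qualify |

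The planned window closes 7 − 2 = 5 days before the sutures come out. No other complication row in Table 1 is restricted to the initial stay. The window also has no fixed length: a patient kept beyond POD 2 is observed for longer, and length of stay is itself a parameter in the same table.

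**2. Illustration of the under-count**

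Inputs:
- N = 200 planned patients (Sample size calculation).
- r = true wound infection rate, **assumed** 1 to 5%.
- f = share of infections that begin by POD 2, **assumed** 0 to 20%.

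Formulas:
- infections occurring = N × r
- infections inside the time window = N × r × f
- chance of counting at least one = 1 − (1 − r × f)^200

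| r | Occurring | f | Inside the window | Chance of at least one |
|---|---|---|---|---|
| 1% | 200 × 0.01 = 2 | 5% | 0.1 | 9.5% |
| 1% | 2 | 20% | 0.4 | 33% |
| 3% | 200 × 0.03 = 6 | 5% | 0.3 | 26% |
| 3% | 6 | 10% | 0.6 | 45% |
| 3% | 6 | 20% | 1.2 | 70% |
| 5% | 200 × 0.05 = 10 | 5% | 0.5 | 39% |
| 5% | 10 | 20% | 2.0 | 87% |

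At f = 0 every count is zero. Over the whole assumed range, 2 to 10 infections occur and the window alone counts 0 to 2. The table applies only the time condition. The laparotomy condition would lower the counts further, by an amount that depends on how investigators read the word.

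**The case against.** Several points on the other side have force.

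- **Other routes of capture.** Adverse events are recorded and scored by CTCAE, complications are graded by Clavien-Dindo with a broad lowest grade, and readmissions are collected with their reasons. A late infection can therefore be in the trial's data while missing from this row. This stands: the defect is in what the outcome counts, and it does not show that safety information is lost.
- **Limited inferential weight.** The protocol says that its data may be too few for a firm safety conclusion, and it puts the emphasis among complications on cardiac events and venous thromboembolism. Even 10 infections would be about 5 per arm. This stands too: a corrected row would describe the infections properly but would not give a well-powered comparison. Low power is still a different matter from a definition that leaves events out.
- **No favoured arm.** The restriction applies to both blinded arms and does not touch the primary hemoglobin endpoint. This stands.
- **Unknown size.** A reader might infer that only patients converted to open surgery could qualify, or that almost no infection would be counted. The documents do not support either statement. Surgical conversion is not mentioned, specimen removal is not described, and the technique is referred to a cited source. If investigators treat an extraction incision as a laparotomy, the first condition could be met in many patients. No onset times are given, and patients with complications may stay past POD 2. Comparing 2 days with 3 months of follow-up does not settle it either, since nothing says that infections are spread evenly over that time.

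None of these points makes the definition fit the operation and discharge day that the article describes.

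**Conclusion.** The point holds as a mismatch between the Table 1 row and the trial's own procedures. Read literally, port-site infections and infections appearing after discharge are outside the wound infection outcome, and a result near zero in both arms would be uninformative about wound infection. That much rests on the text alone.

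The size rests on assumptions. With a rate of 1 to 5% and 0 to 20% of onsets by POD 2, the window would count 0 to 2 of 2 to 10 infections. Neither range comes from the documents.

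The consequence is confined to one secondary outcome. A reader might go further and conclude that the trial will miss these infections altogether, or that it is set up to give false reassurance on safety. The documents do not support that, because other records can hold the events and the protocol itself disclaims a definitive safety conclusion. The row is still worth correcting because the change is small.

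**What to change.** Redefine the row as surgical site infection at any surgical incision (port, extraction or conversion) with onset within 30 days of surgery. This matches the readmission window in the hospital stay row and gives every patient the same counting period whatever the length of stay. Use the POD 7 findings, the readmission records and the 3-month visit as sources. No visit is planned at day 30, so infections between POD 7 and day 30 have to be dated from readmission records or at the 3-month visit.

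**Cost.** One table row and no new visits. The change should be documented as an amendment, with acceptance by the review board and ethics committee if it is judged substantial. Earlier patients need blinded reclassification, which is possible only as far as their case report forms give the site and date of infection; the article does not show that they do.

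**Timing.** The change belongs before unblinding. The last patient was expected by February 1, 2022, so the last 3-month visit would fall around May 1, 2022, before the article appeared on June 18, 2022. If the code has already been broken, report the count under the Table 1 wording and the count under the wider definition side by side, and label the second as post hoc.
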